### Patient and public involvement

The NSW Department of Health, NSW local health districts, secondary school teachers and students were involved in the design of the RT4T intervention.

### Statistical analysis

Statistical analyses will be conducted by an independent statistical analysis service—Clinical Research Design, Information Technology and Statistical Support from Hunter Medical Research Institute. Analyses of the primary (programme reach) and secondary outcomes will be conducted using logistic mixed models (SAS Institute, Cary, North Carolina, USA) for dichotomous outcomes, and ordinal or linear mixed effects regression models for continuous outcomes. The primary outcome (ie, reach) will be collected at the school level and assessed using t-tests. Alpha levels will be set at p<0.025 for the comparisons of the moderate and high support arms against the low support arm. If the p values for the differences between the moderate and high support arms with the low support arm reach this threshold, the moderate and high support arms will be compared at a 5% significance threshold. For student-level outcomes, statistical analyses will be adjusted for the clustering of effects at the class level, as students from each school are nested in classes. Although clustering at the school level is negligible after adjusting for clustering at the class level, we will test this assumption and adjust our analyses for school-level clustering if required. For teacher-level outcomes, clustering will be accounted for at the school level. Two potential moderators of effects will be explored using interaction terms (ie, socioeconomic status of school and school location). School socioeconomic status will be determined using the Index of Community Socio-Educational Advantage (ICSEA), which will be obtained from the MySchool website.^60^ School ICSEA values are determined using student-level parent occupation and education data, school location (ie, remoteness), and percentage of indigenous student enrolment.

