### Sample size calculation

We aim to recruit 90 secondary schools, with 30 schools assigned to each of the three treatment arms. This will include an estimated 261 classes and n=~7800 students across the three arms of the trial. Based on our previous research in secondary schools, we estimate 20% of schools will not provide usable data for our primary outcome at follow-up. As few studies have tested the effects of implementation strategies on the reach of the school-based physical activity interventions, there is little information to guide power calculations. Therefore, we estimated that the low support group will achieve 12.5% reach, while both the moderate and high support groups will achieve 25% reach (ie, between-group difference of 12.5%). Our power calculation is based on 90% power, type 1 error rate of 0.025 and SD of 12%. For the continuous secondary student effectiveness outcomes, we assumed an intraclass correlation coefficient estimate of 0.2. If 10% of schools provide usable data (~780 students), our study will have 80% power to detect significant small-to-moderate effects between the treatment arms.

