### Blinding and randomisation

After teachers have completed the RT4T workshop, schools will be randomised to one of three implementation support arms. Schools will be stratified by school type, socioeconomic status and location and randomised using a random number producing algorithm by an independent statistical analysis service. Data analysis will be conducted by individuals blinded to group allocation.

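### Reach is placed under mixed models and then given t-tests; one school-level analysis, adjusted for the randomisation strata, should be named as primary

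*Protocol article*

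**What the plan says.** Two adjacent sentences of the protocol article's Statistical analysis section deal with reach.

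- The first begins: "Analyses of the primary (programme reach) and secondary outcomes will be conducted using logistic mixed models". It goes on to allot logistic models to dichotomous outcomes and ordinal or linear mixed models to continuous ones.
- The second reads: "The primary outcome (ie, reach) will be collected at the school level and assessed using t-tests".

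The Abstract repeats the mixed-model allocation and does not mention t-tests. Nothing in the article ranks the two methods for reach.

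On randomisation, Blinding and randomisation states: "Schools will be stratified by school type, socioeconomic status and location and randomised using a random number producing algorithm". No sentence says that the analysis of reach uses these factors. Two of them return only as exploratory moderators ("Two potential moderators of effects will be explored using interaction terms (ie, socioeconomic status of school and school location"), and school type does not appear in the analysis section at all.

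On size, the Sample size calculation section gives "We aim to recruit 90 secondary schools, with 30 schools assigned to each of the three treatment arms", expects 20% of schools to lack usable primary data, and states "Our power calculation is based on 90% power, type 1 error rate of 0.025 and SD of 12" per cent. The effect is set thus: "we estimated that the low support group will achieve 12.5% reach, while both the moderate and high support groups will achieve 25% reach".

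**The concern.** There are two linked issues.

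First, the primary outcome is named under two methods. A t-test on school percentages gives a difference in mean reach in percentage points and weights schools equally. A mixed model may differ in effect measure, weighting and p-value. The p-values for reach also decide whether the moderate and high support arms are compared with each other, so the choice carries forward.

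Second, stratified randomisation balances the arms on the stratifying factors and so takes between-stratum variance out of the arm contrast. A plain two-sample t-test still counts that variance as error. If the strata predict reach, its standard error is too large, the test is conservative, and precision that the design has already secured is not used.

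**Working it through.** **Inputs.** From Sample size calculation: difference 12.5 points (25% against 12.5%), SD 12 points, power 90%, alpha 0.025, 30 schools per arm, 20% of schools without usable data. From Statistical analysis: "Alpha levels will be set at p<0.025 for the comparisons of the moderate and high support arms against the low support arm". Sidedness is not stated; two-sided is assumed and tested below. The share of between-school variance in reach explained by the strata (R²) is not in the documents; 0.1 to 0.3 is assumed.

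**Step 1: reproduce the plan's figure.** For an unadjusted two-sample comparison of school-level reach:

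n per arm = 2 × SD² × (z₀.₉₈₇₅ + z₀.₉₀)² / difference² = 2 × 144 × (2.2414 + 1.2816)² / 156.25 = 22.9, so 23. Allowing for loss, 23 / 0.8 = 28.75, so 29, against the stated 30.

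In the other direction, 30 × 0.8 = 24 usable schools per arm. Power is 91.4% by the normal approximation and 89.75% by the noncentral t. One-sided 0.025 or two-sided 0.05 gives 20 per arm, or 25 after loss, which does not reach 30. The stated size therefore matches a two-sided, unadjusted t-test on school percentages.

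**Step 2: effect of ignoring the strata, with perfect balance.** Keep the total SD at 12. The residual SD within strata is 12 × √(1 − R²). The t-test then overstates the standard error by the factor 1/√(1 − R²), and its true error at nominal 2.5% is 2 × [1 − Φ(2.2414/√(1 − R²))].

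| R² | SE overstated by factor | True error of t-test | Simulated power, t-test | Simulated power, adjusted |
|---|---|---|---|---|
| 0 | 1.00 | 2.5% | 90% | 90% |
| 0.1 | 1.05 | 1.8% | 91% | 93% |
| 0.2 | 1.12 | 1.2% | 92% | 95% |
| 0.3 | 1.20 | 0.7% | 93% | 97% |

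The power columns are for the planned 12.5-point difference, with 24 schools per arm balanced over 12 assumed strata (three school types × two socioeconomic levels × two locations), 20,000 runs per setting, and the factors fitted as main effects. Before rounding, the simulated gains are 1.8, 3.4 and 4.4 points. The closed-form values are 91.3/92.6/93.9% unadjusted and 92.8/95.4/97.5% adjusted, gains of about 1.4, 2.8 and 3.6. The gain is thus about 1 to 4 points.

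**Step 3: relax the balance.** The article states neither block size nor number of strata, and it expects 20% of schools to be lost. With assumed blocks of three over 12 strata and 20% random loss, simulated true error of the t-test is about 2.3%, 1.8% and 1.3% for R² of 0.1, 0.2 and 0.3. A second simulation on the same assumptions gave about 1.9%, 1.4% and 1.4%, so these figures are good to roughly half a percentage point. With all 12 cells fitted, adjustment changes power by about −1, +2 and +4 points. Without effective balancing, the t-test's error stays near nominal (2.3% to 2.7%).

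**The case against.** The strongest reply is that the intended analysis can be worked out. The mixed-model sentence is a list by outcome type. Reach is a percentage collected per school, so it does not fall under the logistic part. The following sentence is specific to reach, and the sample size agrees with it. This largely stands. A reader might infer that the plan permits a student-level odds ratio as a rival primary result and leaves the sponsor free to choose. The documents do not support that much. What remains is that the first sentence names reach explicitly and nothing says which statement governs. An analysis plan that is not shown may settle this, but it would have to overrule one printed sentence.

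The second reply is that a school-level t-test is valid, deals with clustering, does not inflate type I error and is the basis of the stated power. All of this stands. The stratification issue is a loss of efficiency of unknown size.

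Two further inferences should be resisted:

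- A reader might take adjustment to raise power from 90% to 93%, 95% or 97%. The 90% applies only when R² is 0. If the strata matter, the unadjusted test under stratified randomisation also gains, to about 91%, 92% or 93%.
- A reader might object that a t-test cannot carry the interaction terms. Nothing says that the moderators are to be explored within the t-test; a separate exploratory model contradicts nothing.

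**Conclusion.** The point holds in a limited form. The text places reach under two methods and should name one. The school-level analysis appears intended, because the sample size reproduces as an unadjusted two-sided t-test.

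That t-test is valid but conservative whenever school type, socioeconomic status or location predicts reach. If they explain 10% to 30% of between-school variance, true error at nominal 2.5% is about 1.8% to 0.7% under perfect balance, and about 2.3% to 1.3% after 20% random loss. The power at stake at the planned difference is small: about 1 to 4 points gained under perfect balance, and from 1 point lost to 4 gained after loss if every cell is fitted. These sizes rest on the assumed R², 12 strata, blocks of three and loss at random. If the strata are unrelated to reach, the t-test costs nothing.

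Neither type I error control nor the planned 90% power is breached. This is a worthwhile clarification and a modest improvement, and it does not threaten the trial's validity.

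**What to change.** In the Statistical analysis section, name one primary analysis of reach: a linear model of school-level reach (%) on arm, adjusted for school type, socioeconomic status and location as used in the randomisation. Enter these as main effects rather than as a full set of cells, because fitting all 12 assumed cells can cost about a point of power when the strata explain little. Report the moderate-versus-low and high-versus-low differences in percentage points with 97.5% confidence intervals, matching the 0.025 level. Remove reach from the mixed-model sentence, or keep that model as a named sensitivity analysis, and bring the Abstract into line.

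The cost is a wording change and a few degrees of freedom: four under the assumed coding (two for school type, one each for the other factors). The stratum values are already held from randomisation, so no new data are needed, and the sample size can stand.

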**Objective:**

To compare the effects of three implementation support models on the reach (primary outcome), dose delivered, fidelity, sustainability, impact and cost of RT4T.

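### Testing moderate versus high support only after both arms beat low is stricter than 5% familywise control needs, and costs power on the contrast that isolates equipment

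*Protocol article*

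**What the plan says.** The Abstract states the aim as follows: "To compare the effects of three implementation support models on the reach (primary outcome", then lists the secondary outcomes. The arms are cumulative: moderate adds external support to training and resources, and high adds the equipment pack to that (Table 1; Materials and equipment). Moderate versus high is therefore the only contrast that isolates equipment.

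The Statistical analysis section gives the testing rule in three parts:

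- Test: "The primary outcome (ie, reach) will be collected at the school level and assessed using t-tests".
- First step: "Alpha levels will be set at p<0.025 for the comparisons of the moderate and high support arms against the low support arm".
- Second step: "If the p values for the differences between the moderate and high support arms with the low support arm reach this threshold", then "the moderate and high support arms will be compared at a 5% significance threshold".

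The word *both* does not appear. The plural p values, and the naming of the two arms together, make it the natural reading.

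On size, the Sample size calculation section says "we estimated that the low support group will achieve 12.5% reach, while both the moderate and high support groups will achieve 25% reach" and "Our power calculation is based on 90% power, type 1 error rate of 0.025 and SD of 12" percent, with 30 schools per arm and 20% of schools expected to give no usable primary outcome data.

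**The concern.** Suppose high support beats low and moderate does not. On the natural reading the plan then does not allow a confirmatory test of high against moderate. That is a situation in which a reader would most want to know whether equipment made the difference. The two comparisons with low cannot stand in for the missing test, because one significant result beside one non-significant result does not show that the two arms differ.

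At stake is power for one of the three pairwise comparisons that the objective implies. The question is whether the strict gate is needed to protect the error rate.

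**Working it through.** **Inputs.** From the Sample size calculation section: SD 12 points; difference 12.5 points (12.5% against 25%); type 1 error 0.025; power 90%; 30 schools per arm; 20% loss, so 30 × 0.8 = 24 analysable schools per arm. From the Statistical analysis section: t-tests on school-level reach; 0.025 for each comparison with low; 0.05 for moderate versus high. Assumed, because not stated: two-sided tests and normally distributed school-level reach.

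**Reproducing the plan's own figure.** n per arm = 2(z₀.₉₈₇₅ + z₀.₉₀)² × SD² / difference² = 2 × (2.241 + 1.282)² × 144 / 156.25 = 22.9, so 23. Then 23 / 0.8 = 28.75, so 29, against the stated 30. A one-sided 0.025 gives 20, or 25 after inflation, so two-sided is the reading that fits. At 24 schools per arm, exact t-test power is 89.8%.

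**Is the gate needed for error control?** The three null hypotheses are moderate = low, high = low and moderate = high.

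1. If any two of these are true, so is the third. The only intersection of them is therefore the global null, that all three arms are equal.
2. Closed testing allows a pair to be rejected at 5% if the global null is also rejected by a 5% test.
3. Rejecting when either comparison with low has p<0.025 is a valid 5% test of the global null (Bonferroni, 2 × 0.025 = 0.05). The plan's first step already does this.
4. So once either comparison passes, moderate versus high may be tested at 5% with strong familywise control. Requiring both is sufficient but not necessary.

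**What it costs.** Simulation with 200,000 trials per scenario, 24 schools per arm, SD 12, two-sided t-tests. Entries are the probability of declaring that high differs from moderate.

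| True reach, low/moderate/high | Plan's gate opens | Plan (both) | Either |
|---|---|---|---|
| 12.5/12.5/25 | 1.9% | 1.5% | 87% |
| 12.5/17.5/25 | 20% | 6% | 54% |
| 12.5/18.75/25 | 31% | 7% | 41% |
| 12.5/25/37.5 | 90% | 84% | 94% |

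In the first row, high passes and moderate fails in about 88% of trials (89.8% − 1.9%). An ungated 5% t-test at 24 per arm has 94.2% power for 12.5 points, so for a difference of that size the gate limits the test, not the sample.

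**Error rates.** Under the global null, familywise error is 4.6% with either rule, because in both cases a false rejection needs a comparison with low to pass 0.025. At 12.5/25/25, where moderate = high is true, the false rejection rate for that pair is 2.9% under the plan and 4.9% under *either*.

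**Optional extension.** The same argument allows the remaining comparison with low to be tested at 0.05 once the other has passed 0.025. At 12.5/25/25, both arms then beat low in 89% of trials against 83% under the plan. At 12.5/12.5/25, the false rejection rate for moderate versus low rises from 2.5% to 4.5%.

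**The case against.** The strongest reply is that nothing here is an error. The rule controls familywise error, the Abstract ties the 0.025 level only to comparisons with low, and the trial was sized with moderate and high both at 25%, so no difference between them was planned. Asking both enhanced arms to beat usual practice before comparing them is a recognisable conservative choice. All of that stands. It shows that the rule is valid, but not that its strictness is needed, and the plan does prespecify the comparison.

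Three other points stand and limit the finding:

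- The 1.5% against 87% contrast assumes that external support adds nothing, contrary to the sample size assumption. If support works as assumed and equipment adds as much again, the loss is 84% against 94%.
- *Both* is inferred. If *either* was meant, the loss on moderate versus high disappears.
- The more powerful rule is not free. False rejections become more frequent, although within the 5% limit.

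A reader might infer that the plan cannot say anything about equipment whenever equipment is worthwhile. The documents do not support that. The gate mostly opens when support is also effective. It restricts a confirmatory claim and does not bar reporting the difference with an interval. The Economic evaluation section presents costs and outcomes across all three arms with no gate attached.

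**Conclusion.** The point holds as an avoidable loss of power, not as a failure of error control. On the natural reading, the condition for testing moderate versus high is stricter than a 5% familywise rate requires. The loss depends on how far external support alone raises reach: from 87% to 1.5% if not at all, from 54% to 6% if by 5 points, and from 94% to 84% if by the planned 12.5 points with equipment adding another 12.5.

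The closure argument needs only that each pairwise test is valid at its level. The percentages also rest on 24 schools per arm, a common SD of 12 points, normality and two-sided tests.

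**What to change.** State that moderate versus high is tested at 5% if either comparison with low reaches p<0.025, and set this before outcome data are seen. Both comparisons with low can stay at 0.025. If this was already the intention, the same edit makes it clear.

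Optionally, state also that once one comparison with low passes 0.025, the other is tested at 0.05. That part would require matching edits to the 0.025 wording in the Abstract and in Statistical analysis, and it is not needed for the equipment question.

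The cost is one sentence for the main change and no extra schools. The price is the higher false-rejection rates shown in the working (2.9% to 4.9% for moderate versus high; 2.5% to 4.5% for moderate versus low if the optional step is taken), all within the 5% familywise limit.

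### Student-level models include school, the randomised unit, only if a pre-test requires it, so their type I error can exceed the nominal 2.5% when the test misses real school variance

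*Protocol article*

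**What the plan says.** Under Blinding and randomisation, the unit of allocation is the school: "After teachers have completed the RT4T workshop, schools will be randomised to one of three implementation support arms". Under Sample size calculation, the numbers are: "We aim to recruit 90 secondary schools, with 30 schools assigned to each of the three treatment arms".

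Under Statistical analysis, three statements govern clustering:

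- Student-level outcomes: the default adjustment is for class, on the ground that each school's students are grouped into classes.
- School, for those same outcomes: "Although clustering at the school level is negligible after adjusting for clustering at the class level, we will test this assumption", followed by a commitment to "adjust our analyses for school-level clustering if required". No figure or source supports the word negligible, and neither the test nor its threshold is named.
- Teacher-level outcomes: "For teacher-level outcomes, clustering will be accounted for at the school level", with no condition attached.

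For the continuous student outcomes, Sample size calculation says "we assumed an intraclass correlation coefficient estimate of 0.2" but does not say whether this is a class or a school ICC.

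**The concern.** Support is given to whole schools. Any variance between schools beyond that between classes therefore enters the comparison of arms in full, and having more classes or students in the same schools does not average it away. A model with class only counts classes from one school as independent replicates of the arm. That makes the standard error too small and the degrees of freedom too many.

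Making the school term depend on a test does not remove the problem. With few schools such a test has little power, so a non-significant result is weak evidence that school variance is absent. The design also gives reasons to expect some. Schools are stratified by type, socioeconomic status and location, and classes in one school share a champion and, in two arms, a project officer.

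At stake are the p values and confidence intervals for student fitness, muscle-strengthening participation and skill competency. These are the trial's effectiveness evidence and also feed the cost-consequence scorecard.

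**Working it through.** **The plan's own figures.** The primary sample size reproduces. A difference of 12.5 points, SD 12, two-sided alpha 0.025 and 90% power need 23 schools per arm by the normal formula, and 23/0.8 rounds up to 29. By the noncentral t, 24 per arm give 89.8% power, and 24/0.8 = 30, as stated. The student-level claim of 80% power for small-to-moderate effects cannot be reproduced, because no effect size or ICC level is given.

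**Inputs from the protocol.** 261/90 = 2.9 classes per school and 7800/261 = 29.9 students per class. Total ICC is 0.2. Sample size calculation expects student data from 10% of schools (about 9, or 3 per arm); Impact evaluation expects them from 10% of the sample. Both give about 780 students.

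**Assumptions, since the protocol gives none.** The ICC of 0.2 is split into school variance v_s and class variance v_c, with residual v_e = 0.8. Each school supplies K = 3 classes. The pre-test is an F test for school at 5%.

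**Step 1, standard error.** With m students per class, let t = v_c + v_e/m. Approximately,

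true SE / class-only SE = √[(K·v_s + t)/(v_s + t)].

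Nine schools give 27 classes, so m is about 29 and v_e/m = 0.0276.

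- v_s = 0.05, v_c = 0.15: √(0.3276/0.2276) = 1.20.
- v_s = 0.10, v_c = 0.10: √(0.4276/0.2276) = 1.37.

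**Step 2, power of the pre-test.** With nine schools in three arms, the F test has 9 − 3 = 6 and 9 × 2 = 18 degrees of freedom, and its 5% critical value is 2.66. The expected mean squares have ratio r = (K·v_s + t)/t, so power = P(F(6,18) > 2.66/r).

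- v_s = 0.05: r = 0.3276/0.1776 = 1.845, power 25%.
- v_s = 0.10: r = 0.4276/0.1276 = 3.351, power 59%.

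**Step 3, type I error at nominal 0.025.** These come from 40,000 simulated balanced three-arm trials per scenario, for one comparison with the low support arm, nine schools:

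| School ICC | SE ratio | Pre-test detects | Class only | Written rule | School always in |
|---|---|---|---|---|---|
| 0 | 1.00 | 5% | 0.025 | 0.024 | 0.026 |
| 0.01 | 1.04 | 8% | 0.031 | 0.029 | 0.025 |
| 0.02 | 1.08 | 11% | 0.040 | 0.036 | 0.026 |
| 0.05 | 1.20 | 25% | 0.068 | 0.055 | 0.027 |
| 0.10 | 1.37 | 59% | 0.118 | 0.062 | 0.024 |
| 0.15 | 1.52 | 88% | 0.177 | 0.045 | 0.026 |

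A separate simulation of the nine-school design gave 0.053 and 0.066 for the written rule at school ICC 0.05 and 0.10, so I quote 0.05 to 0.07.

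**Step 4, more schools, the same 780 or so students.** Over the same range of school ICC, the written rule peaks at 0.037 with 30 schools (3 classes of 9) and at 0.029 with 90 schools (3 classes of 3). In both cases the peak is at school ICC 0.05.

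**The case against.** The strongest defence is that the plan does not ignore school. It commits to testing for school clustering and to adjusting where needed, and the form of the test is ordinary SAP detail. That is fair as to the missing threshold, but the article states the conditional rule itself, and no choice of threshold stops the randomised unit from being conditional.

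Four stronger readings are tempting and are not supported:

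- *The student-level standard errors are too small, full stop.* They are not if school variance beyond class is zero (0.024 in the table) or if each school supplies one class, when class and school coincide. The 2.9 classes per school are programme classes; the protocol does not say how many will supply fitness data.
- *False positives become up to four or more times as likely.* That describes a class-only analysis (0.118/0.025 = 4.7 at school ICC 0.10). The plan prescribes test-then-adjust, for which the same scenario gives 0.062/0.025 = 2.5.
- *Nine schools is a settled number.* Sample size calculation implies it, but the wording in Impact evaluation allows the students to be spread over many more schools, where the excess is small.
- *The trial's main conclusion is at risk.* Reach is analysed at school level and teacher outcomes adjust for school. The protocol already lists the student data as a limitation.

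What stands after this is that the rule never controls error materially better than always including school, and in the protocol's own nine-school scenario it does clearly worse at moderate school ICCs.

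**Conclusion.** The concern holds in conditional form, as a should-fix. Error is inflated when three things coincide: non-zero school variance, more than one class per school, and a test that misses the variance. On the assumptions above, with about nine contributing schools and a school ICC of 0.05 to 0.10, the written rule's type I error is roughly 2 to 2.5 times the nominal 0.025. It is at most about 0.04 with 30 contributing schools and about 0.03 with 90. The split of the ICC and the 5% pre-test level are mine, so these sizes are illustrative. The direction does not depend on them. Only the secondary student impact outcomes are affected.

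**What to change.** Delete the test-then-adjust rule. In every student-level model, include a random intercept for school, with class nested in school, whatever its estimate or p value, and use Kenward-Roger or Satterthwaite degrees of freedom. If only a few schools per arm supply data, analyse school-level summaries instead.

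This changes analysis wording and needs no new data. The cost is wider confidence intervals and lower power for student outcomes, so the 80% power statement should be rechecked and the level of the 0.2 ICC stated. As a guide, with 260 students per arm, ICC 0.2, two-sided alpha 0.025 and 80% power, the detectable standardised difference is 0.70 if the ICC applies to classes of 30. If it applies to schools, the difference is 1.15 with 87 students in each of nine schools and 0.43 with 8.7 in each of 90. The protocol should also reconcile 10% of schools with 10% of the sample, because the size of both problems depends on it.
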